### Choice of Chemotherapy Regimens

Among the different solid tumour types, gastrointestinal (GI) tumours are one example of an appropriate solid tumour type for an initial trial with CURATE.AI. This is because they are the most prevalent (34), and they also form a significant proportion of tumours with raised levels of serum tumour markers (35), which can serve as an input for CURATE.AI. Therefore, we intend to initially recruit patients with GI tumours for this pilot clinical trial, though the eligibility criteria below permit the recruitment of patients with other solid tumour types.

We chose capecitabine-containing regimens (XELOX, XELIRI and single-agent capecitabine) as capecitabine is one of the most commonly used drugs for a wide range of GI and other solid tumours (36), which facilitates recruitment. In addition, it is generally accepted that the MTD for capecitabine is not well-tolerated in a large proportion of patients (37, 38), with guidelines recommending a starting dose lower than the MTD (39). Furthermore, previous studies have established inter-ethnic differences in tolerability profiles for capecitabine (40). Therefore, patients receiving capecitabine require a personalised approach and may benefit from CURATE.AI dose guidance.

During the trial, participants will receive the treatment in 3-week cycles, according to standard dosing schedules for each regimen (**Figure 2**) (41–43). In this pilot clinical trial, CURATE.AI will only modulate capecitabine doses while the remaining drugs (oxaliplatin in XELOX, and irinotecan in XELIRI regimens) will be held constant or adjusted at the clinical investigator's discretion, as per standard-of-care. Additionally, CURATE.AI will only modulate capecitabine doses between cycles and not within a cycle. The drugs used in these regimens will be subjected to the same storage and accountability conditions as per standard-of-care institutional requirements.

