#### CURATE.AI Built-In Safety Mechanisms

All doses recommended by CURATE.AI will always be within the safe dose range pre-specified by the clinical investigator: (1) the predetermined safety range (50–100% of dose used in standard-of-care treatment) and (2) participant-specific dosing range (accounting for the specific participant's personal medical history and clinical context). If CURATE.AI is unable to recommend a dose that fulfils the above requirements, it will not recommend a modulated dose and the clinical investigator will decide the dose according to the standard-of-care. Should the participant experience clinically relevant grade 3 or 4 non-haematological toxicity at a particular dose, we will restrict the next dose recommendation by CURATE.AI to a lower dose. Clinical investigators will have the final say on whether to use the CURATE.AI-recommended dose. Clinical investigators may also adjust the dose beyond CURATE.AI's recommendations as they deem necessary.

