#### CURATE.AI Calibration-Intent Dose Recommendations

For every participant, CURATE.AI will undergo an initial calibration stage (Figure 1, Steps 1–4) with the aim of generating a personalised CURATE.AI profile based on that participant data only. CURATE.AI will provide calibration-intent dose recommendations (Figure 1, Step 1) to collect data on the participant's phenotypic response (measured by tumour markers e.g., CEA, CA19-9) to a range of drug doses (Figure 1, Step 2). Any dose recommended by CURATE.AI to the clinical investigator will always be within the pre-specified safe dose range.

CURATE.AI requires a minimum of three unique data pairs (capecitabine dose and tumour marker), with one data pair collected per cycle, to generate the personalised CURATE.AI profile (Figure 1, Step 3) based on a second-order polynomial. After giving participants capecitabine at calibration-intent doses and measuring the corresponding tumour marker levels, we will analyse the data to determine if they fulfil calibration requirements. If not, CURATE.AI will make further calibration-intent dose recommendations and more data pairs will be collected until the CURATE.AI profile can be generated.

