**Secondary Outcome Measures**			
Patient adherence^b^	>90%	10–90%	<10%
Timeliness of CURATE.AI dose recommendations to the physician^c^	100%	10–99%	<10%
Physician adherence^d^	>70%	10–70%	<10%
Clinically significant dose changes^e^	>20%	1–20%	0%

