*percentage of participants in whom the CURATE.AI-guided cumulative dose is substantially (≥10%) different from the projected standard-of-care cumulative dose, which is defined as the maximum dose of capecitabine (1,000 mg/m^2^ twice daily for XELOX and XELIRI regimen, 1,250 mg/m^2^ twice daily for single agent capecitabine regimen) multiplied by the number of completed chemotherapy cycles.*

f
*defined as the clinical investigator deeming that the patient will not benefit any further from the chemotherapy regimen and considering stopping it, at the time of the first radiological assessment performed as per standard-of-care.*

g
*of grades 3–4 based on Common Terminology Criteria for Adverse Events (CTCAE) version 4.0.*

*ctDNA, circulating tumour DNA*.

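### Table 1 footnote e measures dose change against the maximum capecitabine dose over all completed cycles, so a Green does not by itself show that CURATE.AI dosing differs from standard of care

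*Protocol article*

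**What the plan says.** The Primary Objective section lists three technical-feasibility questions. The third asks whether the dose CURATE.AI recommends is substantially different from the standard-of-care dose, and it points to Table 1 footnote e for the definition.

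Footnote e defines the outcome as the "percentage of participants in whom the CURATE.AI-guided cumulative dose is substantially (≥10%) different" from a reference, namely "the projected standard-of-care cumulative dose, which is defined as the maximum dose of capecitabine" (1,000 mg/m² twice daily for XELOX and XELIRI, 1,250 mg/m² twice daily for single-agent capecitabine), "multiplied by the number of completed chemotherapy cycles". No cycle is excluded. Table 1 rates the outcome Green above 20%, Yellow at 1–20% and Red at 0%.

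Four other statements bear on this definition:

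- Choice of Chemotherapy Regimens says that many patients tolerate the MTD of capecitabine poorly, "with guidelines recommending a starting dose lower than the MTD".
- The Introduction says that conventional practice cuts the dose when toxicity occurs.
- CURATE.AI Built-In Safety Mechanisms confines recommendations to "the predetermined safety range (50–100% of dose used in standard-of-care treatment") and to a participant-specific range.
- CURATE.AI Calibration-Intent Dose Recommendations states that "CURATE.AI requires a minimum of three unique data pairs (capecitabine dose and tumour marker), with one data pair collected per cycle". The stated purpose of these doses is to collect response data over a range of doses.

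**The concern.** The question concerns the dose a participant would receive under standard of care. The yardstick is a fixed ceiling. A participant dosed exactly as in usual care, but averaging 90% of the ceiling or less, counts as a clinically significant dose change although CURATE.AI has changed nothing. Calibration works in the same direction: the three dose levels must differ and none may exceed the ceiling, so at least two lie below it.

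Footnote e is the only measure that the Primary Objective section names for question 3. Trial Design lists the dose difference among the more pressing feasibility issues and uses those issues to justify a single arm. If Green on this row is read as evidence of a dosing contrast, the sponsor could plan an RCT whose arms receive more similar doses than the pilot suggested.

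**Working it through.** The article gives no operating characteristic for this criterion, so there is no figure to reproduce.

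**Inputs from the article.** Participant threshold: at least 10% different (footnote e). Green: more than 20% (Table 1). Planned participants: 10 (Sample Size). Recommended doses: 50–100% of standard. Calibration: at least three cycles, one data pair each. Cycle length: 3 weeks, for at most 12 months.

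**Assumed inputs.** The article gives no calibration doses, no numbers of completed cycles and no usual-care dose intensity. These are varied below and are illustrations, not proposals.

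**Step 1: what Green requires.** With 10 participants, more than 20% means at least 3.

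**Step 2: participant rule.** Let f_i be the dose in cycle i as a fraction of the maximum, and N the number of completed cycles. With no dose above the maximum, a participant is flagged when (Σ f_i)/N ≤ 0.90, that is, when the total shortfall is at least 0.10 × N cycles.

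**Step 3: ordinary reductions alone.** Constant usual care at 80% of maximum is a 20% difference, hence flagged; at 95% it is 5%, hence not flagged. If usual care gives k full-dose cycles and then 75% of maximum, the condition is 0.25 × (N − k)/N ≥ 0.10, so k ≤ 0.6 × N. The participant is flagged if the reduction comes after no more than 2 of 4, 3 of 6 or 4 of 8 cycles.

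**Step 4: calibration alone, with every later cycle at 100%.** The shortfall is 3 minus the sum of the three calibration fractions, and a flag needs N ≤ shortfall/0.10.

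| Assumed calibration doses | Shortfall (cycles) | Limit on N | Flagged when N is |
|---|---|---|---|
| 100/75/50% | 0.75 | 7.5 | 3 to 7 |
| 100/90/80% | 0.30 | 3.0 | 3 only |
| 100/95/90% | 0.15 | 1.5 | never |

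For 100/75/50%, the ratio is 2.25/3 = 0.75 at 3 cycles, 3.25/4 = 0.8125 at 4, 5.25/6 = 0.875 at 6, and 7.25/8 = 0.906 at 8, which is no longer flagged.

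If the three calibration doses are instead drawn uniformly from 50–100% and full dose follows, simulation gives a flag probability of 0.96, 0.92, 0.72, 0.43 and 0.04 at 3, 4, 6, 8 and 12 cycles. The chance of Green is then about 100%, 100%, 99.9%, 87% and 0.5%.

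**Step 5: chance of Green with no CURATE.AI effect.** Let p be the share of participants who would average 90% of maximum or less under usual care. With independent participants, P(Green) = P(X ≥ 3), X ~ Binomial(10, p).

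| Assumed p | P(Green) |
|---|---|
| 0.10 | 7% |
| 0.20 | 32% |
| 0.30 | 62% |
| 0.50 | 95% |

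Step 5 leaves calibration out. Calibration shortfalls would add to these chances.

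**The case against.** **A fixed reference is understandable.** A single-arm trial observes no control dose, and the article labels its reference as projected and states it openly. The remarks on tolerability and starting dose concern the MTD; the article never says that the values in footnote e are the MTD. Treating them as the same is plausible but is an inference. The Introduction's statement on toxicity reductions does not depend on it, and that alone takes usual care below a full-dose projection in some participants.

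**Calibration belongs to the intervention.** The article calls calibration doses CURATE.AI recommendations, question 3 does not limit itself to efficacy-driven doses, and an RCT arm that calibrates would also deliver those cycles. This stands: dropping calibration outright would be a choice of estimand, not a correction. What remains is that a total mixing both kinds of cycle cannot show which of them produced the difference.

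**Overrides.** Footnote e does not say whether doses changed by the investigator enter the CURATE.AI-guided total, so nothing here rests on them.

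**Consequence.** The outcome is secondary, and the Statistical Analysis section plans descriptive statistics. Applicability, judged by a panel from outside the trial, is the main measure of technical feasibility, and all the data inform whether and how an RCT proceeds.

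A reader might infer that the row turns Green almost automatically, or that Green here is enough to launch an RCT. The article supports neither. The first depends on calibration doses, cycle counts and usual-care intensity that it does not give: closely spaced calibration, or many full-dose cycles afterwards, removes the calibration effect. The second is not stated anywhere.

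**Conclusion.** The point holds in a limited form. The article fixes a comparator that its own description of practice places above the dose many patients would receive, and it counts all completed cycles. A Green on this row cannot separate efficacy-driven CURATE.AI changes from ordinary reductions or calibration, so it does not by itself answer question 3.

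That conclusion follows from the text; its size does not. With no CURATE.AI effect, the chance of Green ranges from about 7% to 95% as the assumed share of participants at or below 90% of maximum under usual care goes from 10% to 50%. The calibration effect ranges from none to flagging everyone who completes 3–7 cycles.

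The criterion should be fixed. It is secondary and descriptive, so the flaw does not undermine the trial as a whole.

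**What to change.** 1. Before each recommendation is released, record the capecitabine dose the investigator would prescribe as standard of care for that cycle.
2. Redefine footnote e as a difference of at least 10% between the CURATE.AI-recommended cumulative dose and the sum of those recorded doses.
3. Report the outcome for all cycles and, separately, for efficacy-driven cycles only. Base any statement about efficacy-driven dose differences on the latter.
4. Keep dose relative to maximum as a descriptive dose-intensity figure, not as a Green criterion.

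None of this alters a participant's treatment. It costs one case-report-form field per cycle and a reworded footnote. The reported percentage will probably be lower, and participants who stop during calibration contribute no efficacy-driven data. The recorded dose is an unblinded judgement by the person who decides on the recommendation. After cycle 1 it is also influenced by the modulated doses already given, so it is an imperfect counterfactual. Even so, it addresses the question the article asks, which the maximum dose does not.

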Though CURATE.AI has already been applied in a variety of clinical settings (23–25), there are currently no prior RCTs of CURATE.AI in patients with solid tumours. Additionally, the temporal resolution of the change in the selected tumour markers, as required for CURATE.AI, has not been yet characterised. We are thus conducting this pilot clinical trial to assess the technical and logistical feasibility of a future RCT, as well as to collect exploratory data on efficacy and toxicity to enable future sample size calculations.

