**Exploratory Outcome Measures**			
Efficacy: (1) Clinical progressive disease^f^ (2) Temporal variation in tumour marker level (3) Maximal reduction in tumour marker level	N.A.	N.A.	N.A.
Clinically relevant toxicities^g^	N.A.	N.A.	N.A.
Data collection and exploratory analysis of CEA, CA19-9, and/or other traditional markers in higher frequency serial measurements after modulated dosing in relation to standard frequency readings and other efficacy measures (e.g., RECIST criteria).	N.A.	N.A.	N.A.
Data collection and exploratory analysis of ctDNA as: (1) a tumour marker in serial measurements at given clinical context and after modulated dosing (2) a potential input for CURATE.AI	N.A.	N.A.	N.A.

*See section on Data Collection, Management and Analysis.*

*
*Green: a future randomised trial is definitely feasible. Yellow: a future randomised trial is possibly feasible if its design is appropriately modified. Red: a future randomised trial is unfeasible in its current form.*

a
*percentage of participants in whom we successfully apply CURATE.AI profile. A decision on whether we “successfully apply” the CURATE.AI profile requires expert judgement and cannot be made based on a purely numerical process. The expert panel will consider the following factors with careful regard for the individual circumstances of each participant: (1) error/variance (biological/analytical) is allows accurate predictions (see section primary outcome measure); (2) profile can be generated sufficiently early for the participant to potentially benefit; (3) dose-dependent relationship is observed; (4) profile is actionable (i.e., fulfils the clinical investigator's pre-specified safety requirements); (5) systemic changes in the participant which require profile recalibration are rare or readily assimilated into the CURATE.AI algorithm.*

b
*percentage of participants who always adhered to the prescribed dose whenever they took their medication, as measured by the standardised pharmacovigilance protocol.*

c
*percentage of CURATE.AI recommendations provided in time for the next chemotherapy cycle, across all participants and cycles.*

d
*percentage of CURATE.AI recommended doses that were used by the clinical investigator.*

e

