#### Secondary Objective

Our secondary objective is to collect preliminary data on efficacy and toxicity as exploratory outcomes for this pilot. Specifically, we will evaluate the incidence of clinically progressive disease, changes in tumour marker levels, and incidence of clinically relevant toxicities. As an exploratory outcome, we will explore the utility of tumour markers such as CEA, CA19-9 and ctDNA in higher-frequency serial measurements with modulated doses. We will also explore ctDNA as an input for CURATE.AI to generate dose recommendations, however we will not use this analysis to prospectively guide dosing. We provide further details in our outcome measures below.

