### Sample Size

Since this is a pilot clinical trial with no precedent data, we did not perform an upfront formal sample size calculation. We intend to first recruit 10 patients and perform an interim analysis using the data generated from these participants, which will include formal power and statistical sample size calculations. Based on these outcomes, we will consider cohort expansion or an RCT.

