#### Secondary and Exploratory Outcome Measures

The secondary outcome measures (Table 1) focus on both technical and logistical feasibility, which constitute our primary objectives. Secondary outcomes include: (1) patient adherence to the prescribed dose; (2) timeliness of CURATE.AI recommendations to the physician in time for the next chemotherapy cycle, across all participants and cycles; (3) physician adherence to CURATE.AI recommended doses; (4) clinically significant dose changes where a participant's CURATE.AI-guided cumulative dose is ≥10% different from the projected standard-of-care cumulative dose.

Exploratory outcome measures (Table 1) mainly relate to efficacy and toxicity, which constitute our secondary objectives. Exploratory outcomes relating to efficacy include: (1) percentage of trial participants with clinical progressive disease defined as the clinical investigator deeming that the patient will not benefit any further from the chemotherapy regimen and considering stopping it, at the time of the first radiological assessment performed as per standard-of-care; as well as (2) temporal variation and (3) maximal reduction in tumour marker level from trial initiation to conclusion. We will also measure clinically relevant toxicities of grades 3–4 as an exploratory outcome, using the Common Terminology Criteria for Adverse Events (CTCAE) version 4.0. Other exploratory outcomes include data collection and exploratory analysis of CEA, CA19-9 and/or other traditional tumour markers in higher frequency serial measurements after modulated dosing in relation to standard frequency readings and other efficacy measures, e.g., RECIST criteria. Finally, we will perform data collection and exploratory analysis of ctDNA as a tumour marker in serial measurements at given clinical context and after modulated dosing, as well as a potential input for CURATE.AI. However, we will not use the analysis of ctDNA to prospectively guide drug dosing in this pilot clinical trial.

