#### Statistical Analysis

We will perform and report descriptive statistics of the outcome measures. We will also perform graphical analyses of the temporal variations in tumour marker level. We will not statistically analyse efficacy and toxicity exploratory outcomes.

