## Conclusions

This protocol describes the design of the PRECISE CURATE.AI pilot clinical trial. To date, drug dosing in oncology lacks personalisation. CURATE.AI opens the possibility of personalised dosing for single- and multi-drug regimens, that is dynamically optimized throughout treatment. Furthermore, it is based on a small data set collected only from the treated individual rather than population data. CURATE.AI may thus overcome the challenges that impede the adoption of big data approaches for personalised drug dosing. This pilot will provide technical and logistical feasibility data, as well as exploratory efficacy and toxicity data for sample size calculations, thus laying the clinical foundation for a future RCT of personalised dosing for precision oncology using CURATE.AI.

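### The exploratory toxicity outcome is capped at CTCAE grade 4, so a fatal (grade 5) toxicity falls outside the one toxicity measure the protocol defines

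*Protocol article*

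**What the plan says.** The toxicity outcome is defined in two places, and they agree.

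- Table 1 lists "Clinically relevant toxicities^g" among the exploratory outcome measures. Footnote g limits it to events "of grades 3–4 based on Common Terminology Criteria for Adverse Events (CTCAE) version 4.0".
- Secondary and Exploratory Outcome Measures: "We will also measure clinically relevant toxicities of grades 3–4 as an exploratory outcome", graded with the same CTCAE version.

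Three other statements show what the outcome is for and how it will be handled.

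- The Secondary Objective is, among other things, to evaluate the "incidence of clinically relevant toxicities".
- The Introduction says the pilot will "collect exploratory data on efficacy and toxicity to enable future sample size calculations". The Conclusions speak of "exploratory efficacy and toxicity data for sample size calculations", and the Abstract makes the same link to power calculations.
- Under Statistical Analysis: "We will not statistically analyse efficacy and toxicity exploratory outcomes". Table 1 gives the outcome no green, yellow or red threshold.

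On cohort size, the Sample Size section says: "We intend to first recruit 10 patients and perform an interim analysis using the data generated from these participants".

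**The concern.** A toxicity measure meant to capture severe events is normally open at the top: grade 3 and above. This one is closed at grade 4. The scale it names has one more step, grade 5, for death related to the adverse event. Read literally, the definition counts a life-threatening toxicity and leaves out a fatal one. Because the upper limit appears in both the table footnote and the main text, it cannot be set aside as a slip in one place.

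At stake is the accuracy of one descriptive figure. If a fatal toxicity occurred without a separate grade 3 or 4 event in the same participant, the incidence named in the secondary objective would be understated, and it would be understated for the most serious kind of event. Anyone who took that incidence forward when planning the randomised trial would start from a figure that is too low.

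**Working it through.** The article states no toxicity rate, so there is no planned figure to reproduce. The check is a comparison of the text, followed by a small illustration.

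**1. Does any wording open the upper end?** Footnote g says grades 3–4, and the outcome section says grades 3–4. Neither says grade 3 or higher, and neither mentions grade 5 or death. The Secondary Objective names the incidence without giving a grade range, so it takes its meaning from those two definitions.

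**2. Does another listed outcome catch a toxic death?** Going through Table 1:

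- The primary outcome concerns successful application of the dosing profile.
- The four secondary outcomes concern patient adherence, timeliness, physician adherence and cumulative dose difference.
- The efficacy outcomes are clinical progressive disease and two tumour marker measures. Clinical progressive disease (footnote f) is an investigator's judgement about further benefit, made at the first radiological assessment. A toxic death before that assessment does not meet it.
- The remaining exploratory outcomes concern more frequent marker sampling and ctDNA.

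None is death or toxic death. The capped toxicity outcome is the only defined toxicity measure.

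**3. Size of the effect on the reported incidence.**

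Inputs: n = 10 (Sample Size section). Assumptions: toxicity is counted per participant; one participant has a grade 5 toxicity with no separately recorded grade 3 or 4 event; no other participant has a qualifying event.

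- Definition as written (grades 3–4): 0/10 = 0%.
- Grade 3 or higher (grades 3–5): 1/10 = 10%.
- Difference: 10 percentage points. In general it is 1/n for each such participant.

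**4. How likely is the situation?** The article gives no fatal toxicity rate, so a range has to be assumed. The chance of at least one fatal toxicity in 10 participants at true rate p is 1 − (1 − p)^10.

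| Assumed p | (1 − p)^10 | Chance of at least one |
|---|---|---|
| 1% | 0.904 | 9.6% |
| 2% | 0.817 | 18.3% |
| 5% | 0.599 | 40.1% |

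These are upper limits for the problem itself, because the count goes wrong only if the participant also has no separate grade 3 or 4 event on record.

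**The case against.** The strongest reply is that a toxic death would not be lost. Study Timeline and Investigations provides for adverse events to be documented for each participant and reviewed before each cycle, with no grade limit. Study Setting and Participant Recruitment commits to monitoring and reporting adverse events even in participants who are unevaluable and replaced. Safety monitoring is set out in a supplement that is not shown and may well cover deaths. This stands. A reader might infer from the definition that a fatal toxicity would vanish from the trial's reports; the article does not support that. The loss is confined to this one count.

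A second reply is that little depends on the count. It has no progression threshold and will not be analysed statistically. This also stands. It is also why no confidence intervals are attached to 0/10 and 1/10 here: they would belong to an analysis the plan excludes.

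Third, a reader might take this count to be the specific figure that feeds the sample size of the randomised trial. The article does not go that far. The Introduction and Conclusions refer to toxicity data in general, and planners could draw on the full adverse event record as well.

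Fourth, the 0/10 versus 1/10 contrast is conditional. The article does not say whether toxicity is counted by participant, by event or by worst grade, and a participant with an earlier grade 3 or 4 episode on record would still be counted. That limits the size of the problem but does not make the boundary right.

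One reply does not stand: that an article may leave such detail to a fuller document. The grade range is not left open. It is stated twice, and what is stated is the problem.

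**Conclusion.** The point holds in a limited form. As defined, the exploratory toxicity outcome excludes grade 5 events, and no other listed outcome takes them in. Where a participant's only qualifying event is grade 5, the incidence is understated by one participant, which is 10 percentage points in a cohort of 10.

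This rests on the CTCAE meaning of grade 5 as death related to the adverse event, on per-participant counting, and on no separate grade 3 or 4 event in that participant. It describes what would happen in that situation; it is not an expected bias in the trial's toxicity rate, for which the article gives no basis.

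The impact is modest. No progression decision turns on the outcome, and the death would probably be visible in general adverse event reporting. The correction is still worth making, because this is the only toxicity measure the article defines and toxicity data are meant to inform the planning of the randomised trial.

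**What to change.** In Table 1, footnote g, and in Secondary and Exploratory Outcome Measures, replace grades 3–4 with grade 3 or higher (grades 3–5). Add that any grade 5 events will be listed separately, so that a fatal event is visible and not merged into a single proportion.

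The grade 3 or 4 wording under CURATE.AI Built-In Safety Mechanisms should stay unchanged. It governs the next dose recommendation for a participant still on treatment and is a different matter from outcome counting.

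The cost is a few words in two places. Adverse events are already to be documented for every participant, and CTCAE grading is already required for this outcome, so no new assessment or visit should be needed.
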